## Abstract

**Background:**

Self-management of diabetes minimizes the risk of macrovascular and microvascular complications, but understanding and/or adherence to self-management recommendations is often suboptimal. DIABEO is a smartphone app (downloaded via the internet) used to calculate bolus insulin doses. A previous study (TELEDIAB 1) showed that the use of DIABEO was associated with a significant improvement in glycemic control in patients with poorly controlled type 1 diabetes mellitus, particularly when combined with teleconsultations with physicians.

**Objective:**

Here, we present the protocol for a new study (Suivi A Grande Echelle d’une cohorte de diabétiques de type 1 et de type 2 sous schéma insulinique basal bolus par la TELEmédecine; abbreviated TELESAGE), conducted in a larger population of diabetic patients with poorly controlled basal-bolus insulin levels.

**Methods:**

TELESAGE is a multicenter, double-randomized, open-label, three parallel–arms study, conducted in approximately 100 centers in France. The study will compare a control group (arm 1: usual follow-up) with two DIABEO telemedicine systems: (1) physician-assisted telemedicine (arm 2), and (2) nurse-assisted telemonitoring and teleconsultations by a diabetologist’s task delegation (arm 3). Initial randomization will allocate the study arms in 12 French regions. A second randomization will assign patients in the groups allocated to each studied region. The primary objective of TELESAGE will be to investigate the effect of the DIABEO telemedicine system versus usual follow-up, with respect to improvements in the glycated hemoglobin levels of approximately 696 diabetic patients with poorly controlled basal-bolus insulin levels.

**Results:**

The TELESAGE study is sponsored by Sanofi (Gentilly, France). A primary completion date is expected in June 2018, and publication of results is expected within 6 months of work completion.

**Conclusions:**

The TELESAGE study is expected to confirm the previous results of the TELEDIAB 1 study using a larger sample of diabetic patients. It is also expected to evaluate a nurse-assisted telemonitoring system. We will assess the potential of the DIABEO telemedicine service in terms of its utility and explore whether it can become an integral part of diabetes care for patients.

**Trial Registration:**

ClinicalTrials.gov NCT02287532; https://clinicaltrials.gov/ct2/show/NCT02287532 (Archived by WebCite at http://www.webcitation.org/6ykajhJKd)

## Introduction

In its first global report on diabetes, the World Health Organization showed that the number of adults living with diabetes has almost quadrupled since 1980 to 422 million adults [1]. Diabetes complications can lead to blindness, heart attack, renal insufficiency, stroke and lower limb amputation. In 2012, diabetes caused 1.5 million deaths [1].

Self-management of diabetes is crucial to minimize the risk of macrovascular and microvascular complications [2,3]. This involves a daily planning of diet and physical activity, proper use of prescribed medication, and self-monitoring of capillary blood glucose levels. All this is done in order to adjust diet, physical activity and insulin treatment. However, adherence to self-management recommendations is often suboptimal, which is of importance for people whose diabetes is poorly controlled [4].

The Scottish registry linkage study [5] shows that only 13%–15% of patients with type 1 diabetes mellitus (T1DM) meet the glycated hemoglobin (HbA_1c_) target level of less than 7.0% [5], whereas more than 20% have very poor glycemic control (HbA_1c_>8.8%). The hazard ratios for death from cardiovascular causes increase from 2.9 in well controlled patients to 10.5 in the poorly controlled ones [6]. The reasons for the insufficient glycemic control among T1DM patients are numerous. T1DM is a complex, relatively infrequent disease that is managed by a diabetologist. The complex rules for calculating insulin doses can lead T1DM patients to inject inappropriate doses, especially during meals, leading to episodes of hypo- or hyperglycemia.

Patients with type 2 diabetes mellitus (T2DM) under intensive basal-bolus insulin regimens face similar problems [7]. An automatic system calculating bolus insulin doses on a daily basis is necessary to help both T1DM and T2DM patients undergoing an intensive insulin regimen. On the other hand, the extreme burden of daily routine (eg, glycemic control, carbohydrate counting, and determining an insulin dose that takes into account additional parameters such as irregular activities or unexpected physical activity) can be reduced through telemedical health care team support when needed. Telemedicine may also help intensively treated T1DM or T2DM patients, often those who are young and/or actively working, who find it difficult to comply with scheduled doctor visits to avoid progressive diabetes control degradation). It is essential for these patients to rapidly contact their caregiver, if necessary by telephone and email. Finally, alerts may help caregivers reach patients when needed.

The DIABEO system was created to overcome some of the above hurdles [8,9]. DIABEO is an app for insulin dosage calculation, available for download on smartphones. It calculates bolus insulin doses according to medical prescription and uses validated algorithms to take into account the carbohydrate intake, predrug glucose and anticipated physical activity reported by the patient. It provides glycemic targets and automatic algorithms for the adjustment of carbohydrate and basal insulin or basal pump rates when plasma postprandial or fasting glucose levels are off target. An internet connection ensures data transmission by means of automatic messages to medical staff (through a secure connection and website) to facilitate remote monitoring and teleconsultations.

In 2009, a pilot study demonstrated the feasibility, safety and accuracy of DIABEO [8]. Moreover, a six-month, open-label, randomized clinical trial conducted in 180 poorly controlled T1DM patients (TELEDIAB 1 study) showed that the DIABEO software combined with short teleconsultations (ie, five minutes every two weeks) demonstrated a 0.91% improvement in HbA_1c_ over controls and a 0.67% reduction when the DIABEO software is used alone [9]. This benefit does not require more medical time and is obtained at a lower overall cost for the patient than usual care [9].

Following the TELEDIAB 1 study, the Haute Autorité de Santé, France (HAS) approved DIABEO as a medical device for use in T1DM patients (July 2016) [10]. DIABEO was approved for two years, and the HAS specified that the renewal will be conditioned on the results of the current study (*Suivi A Grande Echelle d’une cohorte de diabétiques de type 1 et de type 2 sous schéma insulinique basal bolus par la TELEmédecine*; abbreviated TELESAGE).

The purpose of TELESAGE is to investigate the metabolic efficacy of the DIABEO telemedicine service in a large population of patients with poorly controlled diabetes who are on a basal-bolus insulin regimen. Additionally, we will assess its economic impact in terms of cost reduction to the health insurance system. Here, we present the protocol of the TELESAGE study.

## Methods

### Objective

TELESAGE was designed to investigate the efficacy of the DIABEO telemedicine service in improving glycaemic control in a large population of diabetic patients sub-optimally controlled with insulin.

### Study Design

TELESAGE is a randomized, open-label, three parallel-arms study that is to be conducted in approximately 100 public and private centers that employ diabetologists in France (Figure 1). The study protocol was designed by Centre d'Étude et de Recherche pour l'Intensification du Traitement du Diabète (CERITD; Evry, France). CERITD is a nonprofit clinical translational research center located in Corbeil Hospital (Corbeil-Essonnes, France). Selected centers have been already participating in the TELEDIAB 1 study [9]. Voluntis (Suresnes, France) provided the DIABEO software, Orange Telephone Company (Paris, France) provided the smartphone and telephone lines, and Sanofi (France) funded the study.

The study was designed to include a population of approximately 696 T1DM and T2DM patients poorly controlled with a basal-bolus insulin regimen (HbA_1c_≥8%) in real-life conditions. The patient recruitment period was estimated to last approximately 36 months.

The trial compares a control group (arm 1: usual follow-up) with the previously investigated DIABEO telemedicine service (arm 2: software + physician-assisted telemedicine as in the TELEDIAB 1 study [9]) or a new DIABEO telemedicine service (arm 3: software + telemonitoring and teleconsultations delegated by the diabetologists to a nursing staff) (Figure 1). Participants are asked to carry out at least two self-monitoring plasma glucose (SMPG) every day during the study. Patients randomized to arms 2 and 3 receive a smartphone with the DIABEO software. The investigator-physician fixes glycemic targets and associated treatment, alarm values, and values for self-adaptations. Patient enters daily three types of variables in the app: (i) SMPG levels before and after meals (6 measurements) + 1 optional in the night; (ii) carbohydrate counts; and (iii) planned physical activity. Patient entry data is automatically uploaded by the smartphone to a secured website (available to investigators at any time). If fasting or postprandial SMPG do not meet target levels, the system can suggest adjustments for carbohydrate ratio, long-acting insulin analog dose, or pump basal rates.

Following a screening period of 10 days, the main study period will last 12 months, with an optional extension period of at least 12 additional months (Figure 1). If desired, patients from the control group can begin to use the software after 12 months.

#### Physician-Assisted Telemedicine (Arm 2)

Teleconsultations will be conducted with both patients and doctors in front of their computers or smartphone displaying data from the week before. These sessions focused on insulin dose adjustments and motivational support.

**Figure 1 figure1:**
[figure not shown]
Study design. T1DM: type 1 diabetes mellitus; T2DM: type 2 diabetes mellitus.

#### Physician/Nurse Delegation Protocol (Arm 3)

Arm 3 of the study involves a nursing team supervised by a physician, based in Paris and its surrounding region. Figure 2 shows the road map of arm 3, which starts with the investigator-physician, who fixes glycemic targets and associated treatment, alarm values triggering a nurse action, and values for self-adaptations (step 1). A reference nurse performs patient initiations (step 2). The patient can now use the DIABEO app on their smartphone (step 3). The device performs a titration of the insulin dose (and eventually a proposal for dose adaptation) as a function of several factors, including blood glucose levels, physical activity and ingested carbohydrates. The data entered by the patient is sent to a secure platform every 2 hours (step 4). This platform is continuously visible to the referring nurse and the diabetologist. Automatic messages containing analytical data are generated every night (step 5). The referring nurse (who can call the patient and/or the diabetologist, if necessary) analyzes these messages during the morning of each working day. Finally, the diabetologist receives patient data and nursing reports (step 6).

#### DIABEO Software

The DIABEO software was described in the *Introduction* section (for details, see references [8,9]). Telemedicine is similar to that previously described [9], with the exception that patient teleconsultations in arm 3 are conducted by nurses instead of doctors.

#### Clinical Study Flow Diagram

The schedule of visits and measurements is given in Table 1. HbA_1c_ measures assessing glycemic control are performed at visits 1, 2 (optional), 3 and 4.

### Ethical Conduct of the Study and Informed Consent

The study is conducted in accordance with the Declaration of Helsinki and Good Clinical Practice guidelines and in accordance with French privacy law (*Informatique et Libertés*) when processing personal data in the health care field (Act of 6 January 1978, amended by Law No 2004-801 of August 6, 2004).

This clinical trial began after the sponsor had obtained approval from the ethical committee (*Comité de Protection des Personnes* [CPP]; Committee for People Protection) of La Pitié-Salpetrière Hospital (Ile de France VI) and the authorization of the French *Agence Nationale de Sécurité du Médicament* (ANSM; National Agency for Drug Safety). The study was registered under ANSM# 2012-A00072-41. The sponsor communicates all serious and unexpected adverse events to the CPP and the ANSM.

Before inclusion, patients consented to participate in the trial. To that purpose, patients were informed about the nature, objective and possible consequences of the trial, and gave signed consent to participate and release medical-related data.

### Patients

As calculated in the Statistical Analysis section, 696 subjects have been included in the study (the recommended number of subjects per center was 6-8 patients, the inclusion period lasted from April 24, 2013 to May 19, 2016). The trial is currently active, but not completed.

**Figure 2 figure2:**
[figure not shown]
Road map of arm 3. Patient enters daily three types of variables in the DIABEO application (step 3): (i) Self-measured plasma glucose levels before and after meals (6 measurements) + 1 optional in the night; (ii) carbohydrate counts; and (iii) planned physical activity (see text for other technical details). HCP: health care practitioner.

**Table 1 table1:** Clinical study flow diagram; schedule of enrollment, interventions and assessments. EQ-5D: EuroQol five dimension scale; HbA_1c_: glycated hemoglobin.

Conponents	Visit #1	Visit #2	Visit #3	Visit #4^a,b,c^	Visit #5^d^ (Optional extension)
Evaluations	Day 0	Month 6	Month 12	Month 24	End of study
Informed consent	✓		✓^e^	✓^d^	
Inclusion / exclusion criteria	✓				
Medical history	✓				
Demographics	✓				
Concomitant treatments	✓	✓	✓	✓	✓
Clinical examination	✓	✓	✓	✓^a,f^	
Randomization	✓				
Weight	✓	✓	✓	✓	✓
Blood pressure	✓	✓	✓	✓^a,f^	
Last HbA_1c_ values	✓	✓	✓	✓	✓
Questionnaires (EQ-5D)	✓		✓	✓^a,f^	
DIABEO initiation	✓^a,b,f^		✓^c^		
Nursing appointment^a^	✓		✓^e^		
Fixing appointment for visit #3		✓			
Satisfaction questionnaire “DIABEO”			✓^a,f^	✓^a,f^	
Severe hypoglycemia		✓	✓	✓^a,f^	
Symptomatic hypoglycemia (≤15 days before)			✓		
Adverse events	To be reported all throughout the study				
Serious adverse events	To be declared to sponsor within 24 hours (next business day)				
Malfunction of the DIABEO software^f^	To be reported all throughout the study				
Care consumption	To be reported every month by all concerned patients				
Remittance of TELESAGE books	✓		✓^a,f^		

^a^Applicable to group 3 (software + nurses’ telemonitoring and teleconsultations).

^b^Initiation takes place within approximately 10 days after the inclusion visit.

^c^Applicable to patients of group 1 (control) continuing the study after 12 months and using the software.

^d^Applicable to patients wishing to use DIABEO during the extension phase and who have not yet signed a consent for that purpose.

^e^Applicable to patients of group 1 (control) continuing the study after 12 months and using the software + nurses’ telemonitoring and teleconsultations.

^f^Applicable to group 2 (software + physicians’ telemedicine).

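### Table 1 limits DIABEO malfunction reporting to group 2, although group 3 and controls who switch after month 12 also use the software

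*Protocol article*

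**What the plan says.** Table 1 (the clinical study flow diagram) has a row for software malfunctions, to be reported for the whole duration of the study. Its label is "Malfunction of the DIABEO software^f", and f is its only marker. The footnotes that bear on who uses the software are:

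- f: "Applicable to group 2 (software + physicians’ telemedicine"
- a: "Applicable to group 3 (software + nurses’ telemonitoring and teleconsultations"
- c: "Applicable to patients of group 1 (control) continuing the study after 12 months and using the software"
- e: "Applicable to patients of group 1 (control) continuing the study after 12 months and using the software + nurses’ telemonitoring and teleconsultations"

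The adverse event and serious adverse event rows of the same table have no group marker.

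On who uses the software, Study Design states: "Patients randomized to arms 2 and 3 receive a smartphone with the DIABEO software". It adds that controls who wish to may start using it after 12 months. The section on the physician/nurse delegation protocol says of arm 3: "The device performs a titration of the insulin dose".

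**The concern.** DIABEO proposes insulin doses, so a malfunction is worth recording even when no harm follows. The schedule ties the malfunction row to one of the two randomised software arms and gives no reason for leaving out the other. The arm left out is the new service, and the Discussion (Study Rationale) says that the study will validate its delegation protocol. The Introduction says that renewal of the device's approval depends on the results of this study.

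If sites followed the row as printed, group 2 would have a formal malfunction record. Group 3 and the switching controls would have only those malfunctions that surfaced as adverse events. The two software arms could then not be compared on malfunctions, and an empty arm 3 column could be misread as an absence of malfunctions.

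**Working it through.** No arithmetic applies. The question is which patients the row covers, and the check is to resolve the table's markers and set them beside the text.

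1. **Who uses the software.** There are three populations: group 2 and group 3 from randomisation (Study Design), and controls who take it up after month 12 (Study Design; Table 1, footnotes c and e).

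2. **What the malfunction row covers.**

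| Population using DIABEO | Its marker in Table 1 | On the malfunction row? |
|---|---|---|
| Group 2, physician-assisted | f | Yes |
| Group 3, nurse-assisted | a | No |
| Controls using the software after month 12 | c, e | No |

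3. **Can f alone mean all software users?** The table's own usage says no. Where an item concerns both software arms, both letters appear: DIABEO initiation at visit 1 carries a, b and f; the satisfaction questionnaire carries a and f at visits 3 and 4; the TELESAGE books carry a and f at visit 3; and several visit 4 items carry a and f.

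4. **How far does that usage reach?** It directly supports adding a. It does not by itself support adding c and e, because a and f together leave out the switching controls. Their case rests on Study Design and on footnotes c and e, which show them using the same software while still in the study.

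5. **Does another section fill the gap?** None does. Malfunction reporting is not mentioned elsewhere in the article.

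6. **What is still captured?** Adverse events and serious adverse events are reported in all groups throughout. The ethics section adds that the sponsor passes serious and unexpected events to the ethics committee and the national agency. A malfunction that leads to a clinical event in group 3 or in a switching control therefore has a reporting route. What the row as printed leaves out is malfunctions without a clinical event, and a consistent record of device faults as such.

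**The case against.** The strongest reply is that Table 1's markers are too irregular to show an intended exclusion. The visit 4 header carries a, b and c but not f, although cells in that column carry f. Its b is a note on the timing of initiation after inclusion, which does not fit a month 24 visit. The nursing appointment row is labelled for group 3, yet its visit 3 cell is marked for controls. A lettering slip in a condensed table is more likely than a decision to leave out group 3. Sites would have worked from the full protocol and case report form, which are not shown, and inclusion ended in May 2016. This stands as a limit on the consequence: nothing shows that any site left malfunctions unreported. It does not remove the contradiction, because the article states a group restriction and that restriction conflicts with its own text.

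Two stronger readings are tempting, and the documents support neither.

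- A reader might infer that malfunctions in group 3 would go unseen altogether. The unrestricted adverse event rows rule that out for malfunctions causing harm. In arm 3, data are also sent every 2 hours and a nurse analyses the nightly messages each working morning. That is not formal malfunction reporting, but it makes complete invisibility implausible.
- A reader might infer that half of the randomised users are lost and that the upper limit of a malfunction rate doubles. The 1:2 allocation puts about 696 × 2/3 = 464 patients on DIABEO, but the split between arms 2 and 3 is not given. A bound based on zero events also assumes independent failures between patients, which is doubtful for shared software. Nor do the Outcome Measures list malfunction or plan a malfunction rate.

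**Conclusion.** The point holds as an inconsistency in the safety reporting schedule. The malfunction row names one of the three populations using the software, and the other two are established by Study Design, the arm 3 section and the table's own footnotes. Followed literally, it would confine formal reporting of malfunctions without a clinical event to group 2 and make arms 2 and 3 non-comparable on malfunction counts.

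No numerical size can be given from the documents. The primary HbA1c comparison, the sample size and the power are not affected. Whether any data are missing depends on what sites were told, which the article does not show. A deliberate decision to exclude group 3 should not be inferred.

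**What to change.** - Reconcile the malfunction row so that it covers every patient using the software: add a for group 3, and c and e for switching controls, alongside f.
- Check the corrected row against the full protocol and the case report form. If those already require reports from all users, correcting the published table is enough.
- Only if sites were in fact told to report for group 2 alone, query the sites with group 3 patients and switching controls before database lock. State in the study report that arm 3 malfunction counts are incomplete rather than zero.

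The cost is a change of footnote markers and a document check. A site query arises only in the third case. The article describes the trial as active and not completed, so there was still time for this. No new assessment or visit is needed.

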### Inclusion Criteria

Patients enrolled in the TELESAGE study should meet the following inclusion criteria: T1DM and T2DM patient performing self-monitoring of blood glucose (≥2 measured values per day), treated with insulin analogs according to a basal-bolus regimen for at least 1 year and using the same method of administration (pen or pump) for at least 3 months, possessing an Apple or Android smartphone compatible with DIABEO before starting the study, having two HbA_1c_ values ≥8%, one dating to more than 3 months ago and the other less than 1 month ago. Additionally, participants must have the capability to understand and follow the instructions of the study, and be able to provide written consent to participate and specify if they benefit from a social security scheme.

### Exclusion Criteria

Key exclusion criteria included: age <18 years; subject having already used the DIABEO system in the 6 months preceding inclusion, or participating in a clinical trial within 6 months (except Meos, the TELEDIAB 3 study after a 6-month participation period), or treated with human insulin, or pregnant (or wishing to be pregnant during the study period), or subject requiring boluses >0.4 IU/gram (for subjects under functional insulin therapy) or >99 IU per day (for subjects treated on a fixed diet plan), or subject living with staggered hours (eg, night work, meals shifted).

